**Exclusion criteria**
1. Have a history of heart implant device in the last 6 weeks, or have a heart implant device plan or heart transplant plan within the next 12 months
2. Acute coronary syndrome within 6 weeks
3. Severe valvular heart disease, congenital heart disease, severe hypertrophic obstructive cardiomyopathy, acute myocarditis/pericarditis, intracardiac thrombosis, primary pulmonary hypertension, perinatal cardiomyopathy, thyroid heart disease;
4. Implanted pacemaker with no frequency response function, or set the discharge threshold of ICD lower than the heart rate during exercise.
5. Contraindications to exercise training: uncontrolled hypertension (systolic blood pressure >200 mmHg and/or diastolic blood pressure >110 mmHg); Severe arrhythmias such as ventricular tachycardia, frequent multi-source premature ventricular beats, high atrioventricular block and significant QT interval prolongation occurred during exercise test.
6. Progressive dyspnea or loss of exercise endurance in the last 3–5 days at rest;
7. Myocardial ischemia under low power exercise load (<2MET, or <50W);
8. Uncontrolled diabetes;.
9. Recent embolism;
10. Thrombophlebitis;
11. New atrial fibrillation or atrial flutter, etc., and other conditions not suitable for sports training;
12. Severe liver and kidney dysfunction, liver function more than three times the normal value, eGFR <30 mL/min/1.73 m2;
13. Currently suffering from severe mental illness, severe respiratory disorders, severe hematological diseases, severe nervous and neuromuscular diseases, severe metabolic and endocrine diseases, malignant neoplasms, severe autoimmune diseases, complicated with systemic infections and other acute systemic diseases.
14. Other clinical studies have been included to influence the results of this study;
15. Women who are pregnant or preparing to become pregnant, and women who are breastfeeding;
16. The researchers determined that the patients were not suitable for the study.

*BMI, body mass index; LVEF, left ventricular ejection fraction; NYHA, New York Heart Association; ICD, implantable cardioverter-defibrillator; MET metabolic equivalent; eGFR, estimated glomerular filtration rate*.

### Randomization and Allocation

We will use a block- randomization, stratified in groups for center to assign participants to the high- intensity exercise group, moderate- intensity exercise group and the control group in a 1:1:1 ratio. For the hierarchical random assignment operation, the statistical unit responsible adopted the SAS version 9.2 statistical software (procedure 'PROC PLAN') to complete program writing and randomization operations. The random distribution results will be released through the network of a central random distribution system. The results of random allocation will be managed by a person designated by the research group, and the results will be executed independently by clinicians. Due to the interventional study design, blinding is impossible for patients and clinical operators. However, the examiners, researchers collecting data on outcome indicators, data managers, and statisticians will be blinded.

### Intervention and Control

The training program of intervention groups and the control group is shown in Figure 2. The HF-EI trial aims to ensure that patients receive appropriate and stable guide-based care before entering the trial. Throughout the trial, the three groups of patients will receive the usual medications, monthly follow-ups and the same number of visits. This study has a 12-week intervention and a 12-month follow-up period. All interventions and follow-ups will be completed by doctors (obtained a licensed physician qualification) in the Heart Rehabilitation Center.

### Control Group

Patients in the control group will continue to maintain their daily activities (daily activities monitor the number of exercise steps through a sport bracelet) and will not provide additional ET.

### Intervention Group

Patients randomized to receive HIT or MIT training receive 36 supervised training sessions, thrice weekly, in addition to usual care for 12 consecutive weeks of aerobic ET. Patients will be regularly encouraged to exercise on other days. The duration of each exercise session in the high intensity training group is 30 min, and the duration of each exercise session in the moderate intensity training group is 35–42 min. It is estimated that the high intensity training group and the moderate intensity training group have similar energy expenditure (38, 39). Table 2 summarizes the training program for the HF-EI trial. Participants who have serious adverse clinical events during the intervention will immediately stop the intervention measures and withdraw from this clinical study.

**Table 2 T2:** Training program.

**Group**	**Intervention**			
	**Frequency**	**Duration**	**Intensity**	**Form**
High intensity training group	3 times per week	30 min	70% peak VO_2_	Centre-based rehabilitation: treadmill. Home-based cardiac rehabilitation: walk.
Moderate intensity training group	3 times per week	35–42 min	AT	Centre-based rehabilitation: treadmill. Home-based cardiac rehabilitation: walk.
Control group	Daily activities.

*peak VO_2_, peak oxygen consumption; AT, anaerobic threshold*.

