### Outcome Measures

The primary outcome for the HF-EI trial is the change in peak VO_2_ and Minnesota Living with Heart Failure Questionnaire scores (MLHFQ)after 12 weeks. We choose the common primary outcomes in order to obtain the comprehensive effect of different exercise intensities on HFrEF treatment. Aerobic exercise has a well-known positive effect on patients with HFrEF in exercise capacity and quality of life, and peakVO_2_ is an important indicator for evaluating the prognosis of HF (22, 40).

Secondary outcomes included, AT oxygen uptake, 6MWD, LVEF, NT pro-BNP, PHQ-9, GAD-7, all-cause- mortality, hospitalization events for HF, major cardiovascular events, and adverse events.

The test indicators require patients to be measured at the hospital rehabilitation center. The test details are as follows:

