#### Outcome Assessments

Physical examination, exercise steps, medication use, and clinical events (all-cause-mortality, hospitalization events for HF, major cardiovascular events, and adverse events) will receive outpatient follow-up in the 4th and 8th weeks after random assignment. At 12 weeks after randomization, physical examination, laboratory tests, cardiology diagnostic tests, cardiopulmonary exercise test, 6MWD, scale scores, exercise steps, medication, and clinical events will receive outpatient follow-up visits. 4–12 months after randomization, clinical events will be followed up by telephone every month. Both the baseline survey and follow-up will be conducted by two physicians.

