### Statistical Methods

The calculation of the sample size will be based on the primary outcome of the RCT. The sample size calculation was performed using PASS V11.0 (NCSS Company of the United States) with the following calculation formula:

$$\begin{array}{l} n=\Psi^{2}\left[\sum_{i=1}^{k}s_{i}^{2}/k\right]/\left[\sum_{i=1}^{k}{\left({\bar{X}}_{i}-\bar{X}\right)}^{2}/\left(k-1\right)\right]\left(k\;=\;3\right) \end{array}$$

The parameters are set to double-sided α = 0.05, β = 0.1, Power = 1–β = 90%, the average difference in peak VO_2_ of the three groups were 0, 2, 4(ml/kg/min) and the average difference in MLHFQ of the three groups were 2, 12, 10. The corresponding standard difference values of peakVO_2_ were 6, 4, 6 (ml/kg/min) and MLHFQ were 5, 18, 16.

The parameter estimation is based on the results of previous researches (22, 42, 43).

A total of 180 cases were required for the three groups, 60 patients in each group, considering the 20% loss to follow-up rate and stratification factors. Because each of the primary endpoints can be individually reflected in clinical significance. Therefore, if one of the two primary endpoints of the intervention group improves significantly, the study is successful.

Blinded statistical analysis will be performed by qualified statisticians using PASW Statistics 18.0 (IBM SPSS Inc., Armonk, New York, USA). The measurement data will be expressed as mean ± standard deviation (x ± s), measurement data by *t* test, and count data by chi-square test. The clinical events of the treatment groups will be statistically compared, according to the principle of intention-to-treat. The Kaplan–Meier method will be used to calculate the cumulative event rate. The event time of all patients will be measured starting from the randomization time (time zero). We will collect all available information on clinical events until the last patient contact, including patients who withdraw consent or those lost to follow-up. Relative risk (RR) will be calculated using the Cox proportional hazard model. If a sufficient number of events occur, the Kaplan–Meier curve will be used for stratified analysis of the exercise group, and the log-rank test will be used to test the difference in survival. The significance level will be set at *p* < 0.05.

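### After a serious adverse event the protocol ends study participation as well as training, so week-12 primary outcomes are lost and later event follow-up is not assured

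*Protocol article*

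**What the plan says.** All references are to the protocol article.

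- **Intervention Group:** "Participants who have serious adverse clinical events during the intervention will immediately stop the intervention measures and withdraw from this clinical study". This orders two things, an end to training and an end to study participation. The Control Group section has no matching sentence.
- **Outcome Measures:** there are two primary outcomes, peak VO2 and the MLHFQ score, each taken as the change from baseline to week 12. The secondary outcomes include "all-cause- mortality, hospitalization events for HF, major cardiovascular events, and adverse events".
- **Intervention and Control:** all three groups are to have monthly follow-up and equal numbers of visits, and "This study has a 12-week intervention and a 12-month follow-up period".
- **Outcome Assessments:** "4–12 months after randomization, clinical events will be followed up by telephone every month".
- **Statistical Methods:** "The clinical events of the treatment groups will be statistically compared, according to the principle of intention-to-treat", and "We will collect all available information on clinical events until the last patient contact, including patients who withdraw consent or those lost to follow-up". Event times run from randomization and are analysed by Kaplan–Meier and Cox methods.

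**The concern.** Several of the trial's outcome events, such as an HF hospitalization or a major cardiovascular event, are serious events on any ordinary reading. A non-fatal one during training therefore removes the patient from the study that is meant to measure what happens next. Two things follow.

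First, the primary outcomes are read at week 12, the end of the window in which the rule acts. A patient withdrawn in that window has no week-12 value, and the reason is a bad clinical course. Such missingness is informative.

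Second, follow-up for death, readmission and other events stops when the risk has just risen. Kaplan–Meier and Cox analyses assume that censoring is unrelated to risk, and here it would not be.

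If the rule works only in the exercise arms, or if serious events are more frequent in one arm, the loss is unequal. Efficacy and safety comparisons between intensities and against control are then distorted. A larger sample does not remove this, and an analysis plan cannot recover assessments that sites were told not to make.

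**Working it through.** **1. The plan's own figure.** Statistical Methods gives two-sided α 0.05, power 90%, k = 3 and 20% loss. Peak VO2 has means 0, 2, 4 and SDs 6, 4, 6; MLHFQ has means 2, 12, 10 and SDs 5, 18, 16. The stated formula is n = Ψ² × (mean of s²) / [Σ(group mean − grand mean)² / (k − 1)].

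- Peak VO2: mean s² = (36 + 16 + 36)/3 = 29.33; Σ/(k − 1) = 8/2 = 4; ratio 7.33. With Ψ = 2.52 (infinite denominator degrees of freedom), n = 6.35 × 7.33 = 46.6. The exact noncentral F calculation gives 48 per group (power 0.904); 48/0.80 = 60, and 3 × 60 = 180.
- MLHFQ: mean s² = (25 + 324 + 256)/3 = 201.67; Σ/(k − 1) = 56/2 = 28; ratio 7.20; n = 45.7. The exact calculation gives 47 (power 0.903); 47/0.80 rounds up to 59, total 177.

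The stated 180 reproduces, with 48 evaluable patients per group after the 20% allowance. The point does not rest on this calculation; it only supplies the base for step 4.

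**2. The provisions side by side.**

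- A participant withdrawn in, say, week 5 cannot have the same visits as the other groups, and the month 4–12 calls no longer apply to them.
- An intention-to-treat comparison of events needs follow-up of everyone as randomized. A rule that ends follow-up because of an event works against it.
- The sentence on available event information names consent withdrawal and loss to follow-up. It does not name withdrawal after a serious event, it reaches only to last contact (which withdrawal brings forward), and it covers clinical events only. Nothing restores the week-12 peak VO2 or MLHFQ.

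**3. Bias in peak VO2 (illustration).** If a fraction p of an arm is dropped, those kept change by m and those dropped would have changed by d, the arm mean is overstated by p × (m − d). The bias in HIT minus control is therefore p_HIT × (m_HIT − d) − p_ctl × (m_ctl − d).

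Assumptions not in the article: p_HIT = 5, 10 or 15%; p_ctl = 3%; d = −2 ml/kg/min; control at 0. The article lists 0, 2, 4 without naming arms, so HIT is tried at +4 and at +2. The control term is 0.03 × 2 = 0.06.

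| p_HIT | HIT at +4 | HIT at +2 |
|---|---|---|
| 5% | 0.30 − 0.06 = 0.24 | 0.20 − 0.06 = 0.14 |
| 10% | 0.60 − 0.06 = 0.54 | 0.40 − 0.06 = 0.34 |
| 15% | 0.90 − 0.06 = 0.84 | 0.60 − 0.06 = 0.54 |

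With HIT at +4 the contrast is 4 units, so the bias is 0.24/4 = 6% to 0.84/4 = 21% of it. If the rule acts only in the exercise arms, the control term drops out and the first column becomes 0.30–0.90.

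**4. Power.** Suppose 5–15% of each exercise arm is withdrawn on top of the 20% loss, with control at the first listed mean. Evaluable patients per exercise arm fall from 48 to 48 × 0.95 = 45.6 or 48 × 0.85 = 40.8. Power for peak VO2 falls from 0.904 to 0.895–0.872, and for MLHFQ from 0.909 to 0.908–0.905. The loss is small.

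**5. Event follow-up.** The same 5–15% of the 120 exercise patients is 6–18 people. With withdrawal at 6 weeks (1.38 months), survival throughout and a 12-month horizon from randomization, each loses 12 − 1.38 = 10.62 months. The total is 64–191 person-months, all in the exercise arms if the rule applies where it is placed.

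**The case against.** **The event data are partly protected.** The article promises available event information even for patients who withdraw consent, and its wording need not exclude withdrawals made by the investigator. The triggering event is recorded, since time runs from randomization. This stands: a first HF hospitalization is not lost. A reader might infer that later deaths are not counted at all, or that the mortality and safety counts are simply cut off. The article does not support that. What is missing is an assurance of active follow-up after the first event.

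**The arm difference is inferred from a heading.** The sentence speaks of participants in general, and all groups are promised equal visits. This also stands: the loss may differ by arm, but the text does not settle it. That the bias favours the more harmful intensity, or that those withdrawn are the sickest, is plausible, because the Introduction links higher intensity with higher risk. Both remain inferences.

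**Not all the loss is avoidable.** Patients who die have no week-12 values, and some survivors will be unfit for CPET. That is correct and lowers the recoverable bias. Many could still complete the MLHFQ, and surviving patients could still be telephoned.

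**Missing-data methods belong in the analysis plan.** True, and their absence is not raised. The point is an explicit instruction that prevents the data from being collected.

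**Conclusion.** The point holds in this form. The Intervention Group section ties stopping training to leaving the study. Followed as written, this loses the week-12 primary outcomes of surviving patients with a serious event and leaves their later events without assured follow-up. It conflicts with the article's provisions on visits, event calls and intention-to-treat.

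The size cannot be fixed from the article, which gives no serious-event rate and does not say which arm has which assumed mean. Under the assumptions shown, the overstatement of HIT minus control is 0.24–0.84 ml/kg/min (HIT at +4) or 0.14–0.54 (HIT at +2), and these are upper figures because they treat every withdrawn patient as measurable. A reader might set 0.84 against the 2-unit step between adjacent arms and report about 40%. That is the wrong denominator: the affected contrast is HIT minus control, 4 units under that assignment, so the maximum is 21%. The main harm is bias and informative censoring, not lost power.

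**What to change.** Leave the rule on stopping training unchanged. Delete the second half of the sentence, which ends study participation, so that it agrees with Intervention and Control, Outcome Assessments and Statistical Methods. State in its place that participants with a serious adverse event, in all three arms:

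- remain in the study;
- attend the week-12 assessments where medically possible, with the MLHFQ as a minimum;
- continue the scheduled event follow-up to month 12;
- are analysed as randomized.

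Handling after withdrawal of consent stays as Statistical Methods already has it.

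The cost is one amended sentence and a few more week-12 visits and telephone calls that are already in the schedule. The article reports that recruitment is under way, so the change is worth making soon: data not collected cannot be recovered later.

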### Adherence

Adherence refers to the degree to which trial participants comply with the intervention plan. Patients need to complete at least 66% of possible supervised training courses before consideration for treatment. The HF-EI trial uses several methods to promote compliance. First, researchers and trainers should regularly encourage patients randomized to ET to participate in supervised training courses. Second, a diary is used to track patient attendance and training to monitor patient compliance throughout the trial.

### Outcome Measures

The primary outcome for the HF-EI trial is the change in peak VO_2_ and Minnesota Living with Heart Failure Questionnaire scores (MLHFQ)after 12 weeks. We choose the common primary outcomes in order to obtain the comprehensive effect of different exercise intensities on HFrEF treatment. Aerobic exercise has a well-known positive effect on patients with HFrEF in exercise capacity and quality of life, and peakVO_2_ is an important indicator for evaluating the prognosis of HF (22, 40).

Secondary outcomes included, AT oxygen uptake, 6MWD, LVEF, NT pro-BNP, PHQ-9, GAD-7, all-cause- mortality, hospitalization events for HF, major cardiovascular events, and adverse events.

The test indicators require patients to be measured at the hospital rehabilitation center. The test details are as follows:

#### Cardiopulmonary Exercise Testing(CPET)

According to the recommendations of international guidelines, CPET will be performed before randomization to determine exercise safety in patients. We will evaluate patient exercise endurance using CPET peak power, exercise duration, peak oxygen uptake, and AT. The core laboratory trains and certifies all researchers performing CPET before recruiting personnel.

#### 6-min Walking Test (6MWT)

Perform 6MWT according to the guidelines of the American Thoracic Society (41). In the room, follow a long and straight corridor and instruct patients to walk back and forth at their chosen walking speed. The corridor is 30 m long, with a mark every 3 m, and turning points are marked with cones. During the test, all patients are guided by a unified standard record.

#### Echocardiography

Echocardiographic images and loops will be digitally recorded and stored on-site for analysis in an assessor-blinded reference echocardiography core lab, using color Doppler ultrasound diagnostic equipment, probe frequency 2.5–3.5HZ. During the examination, the patient assumes the left lateral decubitus position to obtain, the left ventricular long-axis view and the left ventricular short-axis view. The sampling lines are collected at the papillary muscle levels, the level of the mitral valve, and the aortic root to acquire two-dimensional images and an M-shaped spectrum. Echocardiography is repeated 12 weeks after randomization.

#### Laboratory Measurements and Biobanking

After resting for at least 5 min, blood samples will be collected under standardized conditions. According to standard operating procedures, all samples will be centrifuged immediately, aliquoted, and stored at −80 °C. Blood tests will be performed by a locally accredited laboratory.

#### Psychometric Analysis

A validated standard questionnaire will be used to assess the quality of life at baseline with repeat assessments within 12 weeks of patient randomization.

### Data Collections

The HF-EI research data collection process is shown in Figure 2.

#### Baseline Data

We will monitor the demographic data, medical history, physical status, laboratory tests (NT pro-BNP), cardiology diagnostic tests (LVEF), cardiopulmonary exercise tests (peak VO_2_, AT oxygen uptake), 6MWD, scale score(MLHFQ, PHQ-9, and GAD-7)and medications during the baseline period. Baseline data will be collected through outpatient consultation and medical record review.

#### Outcome Assessments

Physical examination, exercise steps, medication use, and clinical events (all-cause-mortality, hospitalization events for HF, major cardiovascular events, and adverse events) will receive outpatient follow-up in the 4th and 8th weeks after random assignment. At 12 weeks after randomization, physical examination, laboratory tests, cardiology diagnostic tests, cardiopulmonary exercise test, 6MWD, scale scores, exercise steps, medication, and clinical events will receive outpatient follow-up visits. 4–12 months after randomization, clinical events will be followed up by telephone every month. Both the baseline survey and follow-up will be conducted by two physicians.

### Statistical Methods

The calculation of the sample size will be based on the primary outcome of the RCT. The sample size calculation was performed using PASS V11.0 (NCSS Company of the United States) with the following calculation formula:

$$\begin{array}{l} n=\Psi^{2}\left[\sum_{i=1}^{k}s_{i}^{2}/k\right]/\left[\sum_{i=1}^{k}{\left({\bar{X}}_{i}-\bar{X}\right)}^{2}/\left(k-1\right)\right]\left(k\;=\;3\right) \end{array}$$

The parameters are set to double-sided α = 0.05, β = 0.1, Power = 1–β = 90%, the average difference in peak VO_2_ of the three groups were 0, 2, 4(ml/kg/min) and the average difference in MLHFQ of the three groups were 2, 12, 10. The corresponding standard difference values of peakVO_2_ were 6, 4, 6 (ml/kg/min) and MLHFQ were 5, 18, 16.

The parameter estimation is based on the results of previous researches (22, 42, 43).

A total of 180 cases were required for the three groups, 60 patients in each group, considering the 20% loss to follow-up rate and stratification factors. Because each of the primary endpoints can be individually reflected in clinical significance. Therefore, if one of the two primary endpoints of the intervention group improves significantly, the study is successful.

Blinded statistical analysis will be performed by qualified statisticians using PASW Statistics 18.0 (IBM SPSS Inc., Armonk, New York, USA). The measurement data will be expressed as mean ± standard deviation (x ± s), measurement data by *t* test, and count data by chi-square test. The clinical events of the treatment groups will be statistically compared, according to the principle of intention-to-treat. The Kaplan–Meier method will be used to calculate the cumulative event rate. The event time of all patients will be measured starting from the randomization time (time zero). We will collect all available information on clinical events until the last patient contact, including patients who withdraw consent or those lost to follow-up. Relative risk (RR) will be calculated using the Cox proportional hazard model. If a sufficient number of events occur, the Kaplan–Meier curve will be used for stratified analysis of the exercise group, and the log-rank test will be used to test the difference in survival. The significance level will be set at *p* < 0.05.

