According to the grading standards for exercise intensity proposed by the 2020 European Society of Cardiology (ESC) Guidelines on sports cardiology and exercise in patients with cardiovascular disease, the anaerobic threshold (AT) intensity is moderate, 70% PeakVO_2_ intensity is high intensity (36). We will design a three-arm randomized controlled experiment to explore the effectiveness and safety of moderate exercise intensity (AT intensity) in the treatment of HFrEF. The HIT (70% PeakVO_2_ intensity) group served as the active control group, and the daily activity group served as the placebo control group. Mainly compare MIT and HIT, or MIT and daily activities, and explore the dose-effect relationship of exercise intensity on changes in clinical outcomes through regression analysis. We assume that MIT has a greater impact in the main results than HIT and daily activities.

We will evaluate the efficacy and safety of different aerobic exercise intensities in patients with HFrEF: the HF-EI trial. This study is the first multicenter randomized controlled trial (RCT) on the effects of different aerobic exercise intensities in patients with HFrEF in China. By collecting data on exercise capacity and exercise rehabilitation, we will evaluate the clinical efficacy of exercise-based CR in Chinese patients with HFrEF. Finally, suitable exercise intensity will be recommended for the popularized HFrEF aerobic exercise program for Chinese patients with HFrEF.

The primary objective of the HF-EI trial is to investigate the effects of different exercise intensities on exercise capacity and quality of life in patients with HFrEF. As secondary objectives, the HF-EI trial will evaluate AT oxygen uptake, 6-min walk distance (6MWD), left ventricle ejection fraction (LVEF), N-terminal prohormone of brain natriuretic peptide (NT pro-BNP), the Patient Health Questionnaire-9 (PHQ-9), General Anxiety Disorder-7(GAD-7), all-cause mortality, HF hospitalization, major cardiovascular events, and adverse events.

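### The stated 90% power belongs to a three-group F test; the planned t test of moderate against high intensity has about 48% power on peak VO2 and 9% on MLHFQ

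*Protocol article*

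**What the plan says.** All the sizing statements stand in the Protocol article, Statistical Methods.

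- Method: "The sample size calculation was performed using PASS V11.0 (NCSS Company of the United States) with the following calculation formula". The formula has k = 3 and divides the average of the three variances by the between-group variance of the means, multiplied by Ψ². This is the one-way analysis-of-variance formula.
- Error rates: "The parameters are set to double-sided α = 0.05, β = 0.1, Power = 1–β = 90" per cent.
- Peak VO2 means: "the average difference in peak VO_2_ of the three groups were 0, 2, 4(ml/kg/min".
- MLHFQ means: "the average difference in MLHFQ of the three groups were 2, 12, 10".
- SDs: "The corresponding standard difference values of peakVO_2_ were 6, 4, 6 (ml/kg/min) and MLHFQ were 5, 18, 16". The values are not assigned to arms.
- Size: "A total of 180 cases were required for the three groups, 60 patients in each group, considering the 20% loss to follow-up rate".
- Success: a significant improvement on either of the two primary endpoints is enough.
- Analysis: "measurement data by *t* test, and count data by chi-square test", at p < 0.05. No three-group test is named for the continuous outcomes.

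The Introduction sets the contrasts: "Mainly compare MIT and HIT, or MIT and daily activities". It also states the expectation that MIT does better than both other arms.

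**The concern.** An F test on three groups asks whether any arm differs from the others. Its power can come almost entirely from the gap between exercise and control, and says little about the gap between the two exercise arms. The article quotes one power figure, for the F test, and then names a different test and pairwise contrasts. A reader will take the 90% to cover those contrasts.

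The Abstract says the trial is to find the appropriate intensity, the Introduction says an intensity will be recommended from it, and the Discussion aims to show the superiority of training at the anaerobic threshold. All three depend on MIT against HIT. If the power there is far below 90%, the trial may well miss the very difference it assumes, and the stated 90% would make that miss look more informative than it is.

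**Working it through.** **Inputs**, all from Statistical Methods: two-sided α 0.05; peak VO2 means 0, 2, 4 with SDs 6, 4, 6; MLHFQ means 2, 12, 10 with SDs 5, 18, 16; 60 per arm and 20% loss, so 60 × 0.8 = 48 evaluable per arm. Assumption: the first value in each list is control.

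**Step 1. Reproduce the plan's figure.** Non-central F with 2 and 3(n − 1) degrees of freedom and λ = n × Σ(mean − grand mean)² / average variance. The printed formula is the same relation with Ψ² = λ/2. The article does not give Ψ, so I used the exact distribution.

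- Peak VO2: Σ = 4 + 0 + 4 = 8; average variance = (36 + 16 + 36)/3 = 29.33; at n = 48, λ = 48 × 8/29.33 = 13.09; power 90.4%. At n = 47 it is 89.7%, so 48 are needed, and 48/0.8 = 60 per arm, 180 in all.
- MLHFQ: Σ = 36 + 16 + 4 = 56; average variance = (25 + 324 + 256)/3 = 201.67; at n = 48, λ = 13.33; power 90.9%. Here 47 are needed, and 47/0.8 rounds up to 59 per arm.

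The 180 is therefore correct for the F test, and peak VO2 drives it. These figures treat the averaged variance as common to all arms. Simulating the F test with the unequal SDs (normal data, 40,000 runs, 48 per arm) gives about 87.5% and 95.6%.

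**Step 2. Power of the t tests.** SE = √[(s₁² + s₂²)/n]; power from the non-central t distribution with Welch degrees of freedom, two-sided 0.05.

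| Endpoint and pair | Difference | SE at 48 | Power at 48 | Power at 60 |
|---|---|---|---|---|
| Peak VO2, 2 vs 0 | 2 | √(52/48) = 1.041 | 48% | 57% |
| Peak VO2, 4 vs 0 | 4 | √(72/48) = 1.225 | 90% | 95% |
| Peak VO2, 4 vs 2 (exercise arms) | 2 | √(52/48) = 1.041 | 48% | 57% |
| MLHFQ, 12 vs 2 | 10 | √(349/48) = 2.696 | 95% | 98% |
| MLHFQ, 10 vs 2 | 8 | √(281/48) = 2.420 | 90% | 95% |
| MLHFQ, 12 vs 10 (exercise arms) | 2 | √(580/48) = 3.476 | 9% | 10% |

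**Step 3. Effect of the missing arm labels.** Swapping the second and third values leaves MIT against HIT at 48% and 9%. MIT against control on peak VO2 is 48% if MIT is the arm at 2 and 90% if it is the arm at 4. On MLHFQ it is 95% or 90%.

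**Step 4. The either-endpoint rule.** MIT against control: at least 90% from MLHFQ alone, under either order. MIT against HIT, if the endpoints are independent: 1 − (1 − 0.476)(1 − 0.088) = 0.52. Whatever the dependence, the value lies between 0.48 (the larger of the two) and 0.56 (their sum).

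**Step 5. Precision for MIT against HIT at 48 per arm.** The 95% half-width is 1.989 × 1.041 = 2.1 ml/kg/min and 1.986 × 3.476 = 6.9 points, against assumed differences of 2 and 2.

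**The case against.** The other side has several good points.

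- **The sample size is not miscalculated.** A reader might infer that 180 is wrong. It is not: it follows exactly from the F test. The fault is a mismatch between the test that was sized and the tests and contrasts that are planned.
- **The low power is not general.** A reader might infer that MIT is underpowered against control too. The documents do not support that. MLHFQ alone gives 90% to 95%, and one endpoint is enough. The 48% for MIT against control on peak VO2 holds under only one reading of the unlabelled values. The Design section also describes the trial as an evaluation of MIT, so it does not rest on MIT against HIT alone.
- **The 9% is one endpoint.** Under the success rule, the chance of some significant difference between the exercise arms is about 52%. That is the fairer single figure, and it is still far from 90%.
- **No passage plans to read a null result as equivalence.** The Introduction and Discussion look for superiority of MIT. Such a reading is a risk to guard against, not something the plan states.
- **The test sequence is commonly left to an analysis plan that is not shown.** This is fair as regards an F test as a compulsory first step, which is a debatable choice. It does not remove the mismatch, because the article itself fixes the 90%, the formula, the t test and the main contrasts.

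**Conclusion.** The point stands for MIT against HIT. The only power the article states is that of a three-group F test under a common averaged variance, and it does not apply to one of the two comparisons the article calls main. Under the plan's own inputs, that comparison has about 48% power on peak VO2 and 9% on MLHFQ at 48 evaluable per arm. Even with no losses, power is 57% and 10%. The assumed differences are no larger than the confidence-interval half-widths.

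MIT against control is adequately powered under the either-endpoint rule at nominal 0.05.

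The result assumes that control is the first listed value, that the listed SDs apply to each arm, and that tests run at an unadjusted two-sided 0.05. Halving α to 0.025 for two endpoints would lower MIT against HIT to 36% and 5%, and MIT against control on MLHFQ to 92% or 84%.

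**What to change.** Keep 180 patients and change the sample-size and analysis text as follows.

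1. Label each assumed mean and SD by arm.
2. State that 90% is the power of the three-group F test per endpoint, at 48 evaluable per arm and under a common averaged variance, and that it does not apply to the pairwise t tests.
3. Print the pairwise powers for the planned t tests, in particular 48% and 9% for MIT against HIT.
4. Either name in the analysis the three-group test that was powered, or keep the t tests and quote their power as the design power. Both are acceptable; the two paragraphs must agree.
5. Report MIT against HIT as an estimate with a 95% confidence interval, and state that a non-significant result is not evidence that the intensities are equal.

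The cost is wording and a less favourable stated power for MIT against HIT. Enlarging the trial instead is hardly realistic. By the normal approximation, 90% power would need 137 evaluable per arm for a peak VO2 difference of 2 (137/0.8, rounded up to 172 with losses) and 1,524 evaluable per arm for an MLHFQ difference of 2. Trial Organization says recruitment is under way, so the change should be made before outcomes are compared by arm.
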